### Sample size and power

Sample size calculation for this study is based on an expected difference of 7% in the proportions of patients not requiring interventions after 7 years between patients undergoing yearly standardised imaging surveillance (75% intervention-free rate^18^) versus those s not undergoing standardised imaging surveillance(82% intervention-free rate^19^). To detect this difference with 90% power and a 0.05 significance level, 719 patients per group are required and 1438 in total. To correct for the fact that the first CTA of approximately 20% of patients is abnormal, 1798 patients (1438/0.8) are needed.^20 21^ In addition, we expect incomplete data in 10% of the patients which results in a total number of 1997 patients (1798/0.9). With this sample size, we can also detect a 3% difference in aneurysm-related mortality with statistical significance. We chose a one-sided significance level (non-inferiority) of 0.05 and for standard proportion a 95% non-aneurysm-related mortality and thus 5% freedom from aneurysm-related mortality after 7 years: 0.95. For equivalence limit difference, we chose an acceptable difference between groups of 3%, in which if differences in aneurysm-related mortality equals 3%, they are considered non-inferior. Test-expected proportion is then equal to the standard proportion 0.97. Thus, the expected difference is 0, calculated with a power of 80%. This results in 653 patients per group and 1306 patients in total. Since the first CTA of approximately 20% of patients is abnormal, 1632 patients (1306/0.8) are needed. In addition, we expect incomplete data in 10% of the patients which results in a minimum of, 1813 patients (1632/0.9) are needed in total.

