## Study objectives

The objective of this study is to evaluate whether imaging surveillance frequency might have been safely reduced in a selected group of EVAR patients, for example, in patients with an asymptomatic or symptomatic infrarenal AAA who underwent EVAR and who had no abnormalities on the 3-month postoperative CTA. The clinical course of a large cohort of patients will be evaluated with follow-up ranging between 6 and 11 years. Baseline patient characteristics, aortic anatomy and details of the operation will be derived from the patient’s medical record. The first milestone during follow-up is the first postoperative CTA. This scan either shows complications such as endoleaks, malposition or migration of the graft, or the absence thereof. All follow-up visits, imaging studies, as well as all interventions after EVAR and outcomes will be registered. Our hypothesis is that patients with less follow-up will have better outcomes regarding the number of interventions and aneurysm-related mortality compared to patients with annual follow-up. Regarding the intervention rates, it is expected that adherence to imaging surveillance may detect more abnormalities triggering re-interventions which in itself may cause additional complications and perhaps even a decrease in survival rates. We hypothesise that the need for routine imaging for patients with no abnormalities at their initial CTA can be decreased.

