### Statistical methods

Differences in baseline characteristics between patients undergoing or not undergoing yearly standardised imaging surveillance by either CTA or DUS, will be analysed using the χ^2^ or Fisher's exact test for categorical variables and the student's t-test or Mann-Whitney test for continuous variables, if appropriate.

The primary endpoints, that is, survival and freedom from intervention will be estimated by Kaplan-Meier survival analysis and differences between groups will be assessed with the log-rank test.

Secondary endpoints such as freedom from aneurysm rupture between patients with and without yearly standardised imaging surveillance will be estimated by Kaplan-Meier survival analysis, and differences between these groups will be calculated with the log-rank test.

Multivariable cox regression analysis will be used to determine survival and the freedom of intervention corrected for age, gender, AAA diameter, ASA classification, neck length, neck angulation and type of endograft. The association between postoperative intervention and the following covariates will be investigated with the multivariate Cox-regression analysis:

Age.Gender.AAA diameter.ASA classification.Neck length (>15 mm).Neck angulation (>60°).Type of endograft.Initial postoperative CTA.

All statistical analyses will be done with SPSS software (IBM, V.25). The level for statistical significance is set at a p value <0.05. The proportion of missing data will be displayed. The missing values will be imputed by multiple imputation techniques if this does not exceed 10%–15% and conduct a sensitivity analysis to investigate the effect of the missing data on the results of the analysis. If missing data on outcome variables exceeds 15%, we plan to perform subgroup analysis.

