## Discussion

The goal of this study is to evaluate whether a reduction in follow-up visits and imaging and thus costs, in patients operated on for an asymptomatic or symptomatic AAA with EVAR is safe. We hypothesise that there will be less interventions and no difference in aneurysm-related mortality in patients with less intensive follow-up. With the results of this study, we aim to provide scientific evidence helping vascular surgeons decide whether less vigilant follow-up after EVAR may be considered for patients classified in the low risk group.

The strengths of the ODYSSEUS study are that it can accumulate the data of a large number of consecutive EVAR patients with a theoretical follow-up of 6 to 11 years, and that it captures all surveillance visits, long-term outcomes and mortality post-EVAR. Moreover, 17 medical centres throughout the Netherlands are participating in this study, including university and general hospitals, thereby reducing selection bias.

An e-survey has been sent to all vascular surgeons participating in the ODYSSEUS study. This shows that yearly imaging surveillance is upheld by most vascular surgeons in the Netherlands. In addition, most physicians agree that yearly imaging frequency can be safely reduced in a specific group of EVAR patients. As support for this reduction in frequency is evident in the Netherlands, the next step will be to study the groups for which it will be safe to deviate from the widely accepted surveillance protocols.

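### Aneurysm-related mortality is sized for non-inferiority with a 3-point margin, but the planned analysis never tests against that margin

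*Protocol article*

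**What the plan says.** All references are to the protocol article.

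- **Sample size and power.** The mortality calculation is a non-inferiority one: "We chose a one-sided significance level (non-inferiority) of 0.05". The reference is "for standard proportion a 95% non-aneurysm-related mortality" at 7 years, with a limit of 3 percentage points, an expected difference of 0 and 80% power. The result is 653 per group. The section adds that "if differences in aneurysm-related mortality equals 3%, they are considered non-inferior".
- **Statistical methods.** The primary endpoints are given as survival and freedom from intervention. They are estimated by Kaplan-Meier, and "differences between groups will be assessed with the log-rank test". Multivariable Cox regression adjusts survival and freedom from intervention for age, gender, aneurysm diameter, ASA class, neck length, neck angulation and endograft type. "The level for statistical significance is set at a p value <0.05". The section mentions no margin, one-sided bound or non-inferiority comparison.
- **Main study endpoint** and **Study procedures.** Aneurysm-related mortality is primary. Study procedures lists all-cause mortality as secondary.
- **Hypotheses.** Study objectives expects that "patients with less follow-up will have better outcomes regarding the number of interventions and aneurysm-related mortality" compared with annual follow-up. The Discussion expects that "there will be less interventions and no difference in aneurysm-related mortality" in patients followed less intensively.

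**The concern.** The study asks whether less imaging is safe, and the mortality sample size is built to answer that by ruling out an excess of 3 points or more. A log-rank or Cox test against zero difference answers another question. Its failure to reach significance does not exclude an excess of any particular size, and the smaller or less balanced the groups, the more easily it fails. The analysis section therefore cannot deliver the conclusion that the sample size was bought for. It also leaves unclear whether its survival endpoint is the sized mortality endpoint at all.

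The sentence on a difference equal to 3% adds to the problem, since it is the only text that says when the groups count as non-inferior, and it puts the margin itself on the acceptable side. At stake is a claim that imaging can be reduced safely, made on a mortality endpoint without the planned control of error.

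**Working it through.** **Inputs.** From Sample size and power: proportion free of aneurysm-related death 0.95, margin 0.03, one-sided alpha 0.05, power 80%, 653 per group; and 719 per group (1438 in all) from the intervention calculation that drives the total. Error rates use a normal approximation for two proportions in place of the log-rank test.

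**1. Reproduce the plan's figure.** n = (1.645 + 0.842)² × 2 × 0.95 × 0.05 / 0.03² ≈ 653 per group, an exact match. The same formula with 0.97 in both groups gives 400, so the 653 rests on 0.95. It presupposes a one-sided 5% test against the margin.

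**2. What that test requires.** With 5% mortality in both groups, SE = √(2 × 0.05 × 0.95 / n), which is 0.0121 at n = 653 and 0.0115 at n = 719. The upper limit falls below 3 points only if the observed excess is below 0.03 − 1.645 × SE: about 1.0 point at 653 and 1.1 points at 719. Power is about 80% and 83%.

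**3. An observed difference of 3 points.** For 5% vs 8%, SE = √[(0.05 × 0.95 + 0.08 × 0.92) / n].

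- n = 653: SE 0.0136; upper limit 0.03 + 1.645 × 0.0136 = 0.052
- n = 719: SE 0.0130; upper limit 0.03 + 1.645 × 0.0130 = 0.051

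Both limits, 5.2 and 5.1 points, are well beyond the margin.

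**4. How often a true 3-point excess (5% vs 8%) would pass under each rule.**

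| Rule | Groups (with / without yearly imaging) | Passes |
|---|---|---|
| One-sided 95% upper limit below 3 points | 653 / 653 or 719 / 719 | 5% (simulated 5.2% at 653) |
| Two-sided 0.05 difference test non-significant | 719 / 719 | 36% |
| Same | 653 / 653 | 41% |
| Same | 618 / 820 (43:57) | 38% |
| Same | 1294 / 144 (90:10, assumed) | 64% |
| Observed difference no more than 3 points | 653 / 653 or 719 / 719 | 50% (simulated 49.7% at 653) |

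The 43:57 split borrows the 43% complete surveillance reported by a study cited under Background and relevant literature and data. The 90:10 split is an assumption used as an unfavourable case; the protocol gives no expected split, and its groups form by observed adherence.

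**The case against.** **The 3% sentence may only describe a sample-size input.** It follows directly on "For equivalence limit difference, we chose an acceptable difference between groups of 3" per cent and stands among other inputs. The word observed does not appear, and the 653 reproduces only if sampling error is counted. This stands: a reader might infer that the protocol adopts an observed-difference rule with a 50% false-pass rate, but the text does not establish that. The figure is conditional. The sentence is still wrong as a description of the margin, because a true difference equal to the margin is where non-inferiority should be declared only 5% of the time.

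**Nothing says a non-significant test will be read as safety.** This is also true, so the 36% to 64% range describes a risk that the plan leaves open, not a stated intention.

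**The analysis is more than a log-rank test.** Adjusted Cox regression is planned too. It does not supply the missing comparison, since no margin is attached to it.

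**An unseen analysis plan may hold the non-inferiority test.** Silence alone would be no finding in a condensed article. Here the article commits its primary endpoints to difference tests and labels one of them differently from its own endpoint sections. That is a conflict in the printed text.

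**The hypotheses are not three incompatible ones.** Expecting no difference fits a non-inferiority design with expected difference 0. Only Study objectives, which expects better mortality, departs from this, and expecting benefit does not rule out a non-inferiority test. This part is a matter of alignment.

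**Conclusion.** The sizing and the analysis do not match. Aneurysm-related mortality is powered for one-sided 0.05 non-inferiority with a 3-point margin, but the analysis section tests differences, never uses the margin, and names survival in place of that endpoint. Followed as written, it cannot support a non-inferiority conclusion. The sentence treating a difference equal to the margin as non-inferior is wrong on either reading.

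The size depends on how results would be used. With a true 3-point excess, reading non-significance as safety would pass 36% of the time at 719 per group (38% at 43:57, 64% at the assumed 90:10), and an observed-difference rule about 50%, against 5% intended. These figures assume 5% reference mortality and the two-proportion approximation.

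Two stronger readings are not supported: that the protocol states an observed-difference rule, and that it intends to treat non-significance as proof of safety. Nor is the 653 at fault; it is correct for a reference proportion of 0.95.

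**What to change.** In Statistical methods:

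- Name aneurysm-related mortality as the primary safety endpoint.
- Analyse it as the difference in 7-year aneurysm-related mortality, without minus with yearly imaging, adjusted for the covariates already listed. Show the unadjusted estimate alongside.
- Declare non-inferiority only if the one-sided 95% upper confidence limit is below 3 points.
- State that a non-significant log-rank or Cox result is not evidence of safety.

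In Sample size and power, replace the sentence on a difference equal to 3% with this rule. In Study objectives, align the mortality hypothesis with Sample size and power and the Discussion.

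No new patients or data are needed. Unadjusted power is about 80% at 653 per group and 83% at 719 if the groups are equal. With 1438 analysable patients it would fall to about 77% at a 30:70 split and 67% at 20:80. The cost is a little extra analysis and a stricter criterion for claiming safety.

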### Background and relevant literature and data

Before initiating the ODYSSEUS study, we conducted a survey among Dutch vascular surgeons to find out if they support the possibility of reducing the frequency of imaging surveillance. In this survey, vascular surgeons reported the main reasons patients did not comply with follow-up visits, that is, they had forgotten the appointment or were prevented by force majeure. Most physicians estimated that less than 10% of their patients had missed one or more follow-up visits post-EVAR. This might be an overestimation of the true adherence to follow-up visits, as these observations are in contrast with a study reporting that only 43% of patients had complete surveillance.^4^

We also asked participating vascular surgeons to upload their standard post-EVAR protocol to investigate if there were differences between centres in the Netherlands. In all centres, imaging took place within the first 3 months after surgery, mostly by CTA. Most centres comply with their own post-EVAR surveillance protocols which have many commonalities with the SVS and ESVS guidelines. Only one centre uses precisely the same post-EVAR surveillance protocol as recommended by the SVS guidelines. Another centre had already reduced follow-up imaging to once every 5 years, using either CTA or DUS as is stated in the new ESVS guidelines.^3^ While vascular surgeons still seem to adhere to their hospital-specific protocol, they do support the need for reducing follow-up by selecting a group of patients for which yearly follow-up can safely be omitted. However, some surgeons indicated that more evidence is needed than is available in the current literature.^6 7^

In studies that have investigated the indications for post-EVAR intervention, it is stated that 61%–98% of interventions were necessary because of symptoms and not because of findings at surveillance imaging. This suggests that post-EVAR surveillance protocols provide no benefit to a large group of patients, as complications occur in between surveillance visits.^8 9^ Imaging surveillance may even lead to unnecessary interventions and it does not appear to be associated with improved survival.^9 10^ We hypothesise that the requirement for routine imaging for patients at low risk can be reduced. However, novel endovascular devices still require more intensive surveillance as the short- and long-term results of those devices remain undetermined.

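### The aneurysm-mortality calculation misstates one input (0.97 for 0.95), inverts the event and calls non-inferiority power an ability to detect a 3% difference; N is unaffected

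*Protocol article*

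**What the plan says.** All the figures are in the protocol article, section Sample size and power.

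- **Intervention endpoint.** 75% v 82% intervention-free at 7 years, 90% power, significance level 0.05: "719 patients per group are required and 1438 in total". Dividing by 0.8 for abnormal first CTAs and by 0.9 for incomplete data gives the planned 1997.
- **Claim for aneurysm-related mortality.** With that sample, "we can also detect a 3% difference in aneurysm-related mortality with statistical significance".
- **Calculation given for it.** "We chose a one-sided significance level (non-inferiority) of 0.05", with "a 95% non-aneurysm-related mortality and thus 5% freedom from aneurysm-related mortality after 7 years: 0.95", and an acceptable difference of 3%. Then: "Test-expected proportion is then equal to the standard proportion 0.97". The expected difference is put at 0 and the power at 80%. The result is 653 per group, 1306 in total, and 1813 after the same two inflations.
- **How the groups arise.** General study design and Study procedures form the two compared groups from observed adherence to imaging at least every 16 months, among patients with a normal first CTA.
- **What is said about adherence.** In Background and relevant literature and data: "Most physicians estimated that less than 10% of their patients had missed one or more follow-up visits post-EVAR". The article doubts this estimate and sets against it a study in which "only 43% of patients had complete surveillance".

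**The concern.** Three things in this section do not fit together.

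1. The standard proportion cannot be 0.95 and also 0.97. With 0.95 as standard and 0.97 as test, the expected difference is not 0. The phrase about 5% freedom turns the event round.
2. Detecting a difference and excluding a margin are different properties. Non-inferiority power computed at a true difference of 0 says nothing directly about the chance of a significant result when a 3-point difference exists. Aneurysm-related mortality is a primary endpoint, the Discussion hypothesises no difference in it, and Statistical methods compares survival by log-rank tests at 0.05. A reader told that 3 points can be detected may take a non-significant test as evidence that less imaging is safe.
3. The 90% and 80% power figures both assume two equal groups, and the design does not control group size.

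**Working it through.** **Step 1. Reproduce 653.** Inputs from the section: one-sided 0.05 (z = 1.645), power 80% (z = 0.842), margin 0.03. With p_S the standard and p_T the test proportion free of aneurysm-related death,

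n per group = (1.645 + 0.842)² × [p_S(1 − p_S) + p_T(1 − p_T)] / (0.03 − (p_S − p_T))², where (1.645 + 0.842)² ≈ 6.18.

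| p_S | p_T | n per group |
|---|---|---|
| 0.95 | 0.95 | 6.18 × 0.095 / 0.0009 = 652.6 → **653** |
| 0.97 | 0.97 | 6.18 × 0.0582 / 0.0009 → 400 |
| 0.95 | 0.97 | 6.18 × 0.0766 / 0.0025 → 190 |

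Only 0.95 in both groups gives the stated figure. Inflation: 1306/0.8 = 1632.5 (stated 1632) and 1632/0.9 = 1813.3 (stated 1813).

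**Step 2. Reproduce 719.** Two-sided 0.05, 90% power, unpooled variance: (1.960 + 1.282)² × [0.75 × 0.25 + 0.82 × 0.18] / 0.07² = 718.6 → **719** (a pooled null variance gives 722). This larger number drives the planned 1997.

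**Step 3. What the mortality calculation delivers.** Non-inferiority power at 0.95/0.95 is Φ(0.03/SE − 1.645), with SE = √(2 × 0.0475/n).

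- n = 653: SE = 0.01206, 0.03/SE = 2.487, power 80%.
- n = 719: SE = 0.01149, 0.03/SE = 2.610, power 83%.

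**Step 4. Power to detect a true 3-point difference at 719 per group** (two-proportion normal test at 0.05).

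| Aneurysm-related mortality | Two-sided | One-sided |
|---|---|---|
| 5% v 8% (harm) | 64% | 75% |
| 5% v 2% (benefit) | 87% | 93% |

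Detecting 5% v 8% with 80% power would take 1059 per group two-sided, or 834 one-sided.

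**Step 5. Unequal groups, 1438 analysable patients.** Unpooled variance throughout, as for 719:

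- interventions: SE = √(0.1875/n_yearly + 0.1476/n_other), power Φ(0.07/SE − 1.960);
- non-inferiority: SE = √(0.0475 × (1/n_yearly + 1/n_other)), power Φ(0.03/SE − 1.645).

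| Yearly : not yearly | Interventions | Non-inferiority |
|---|---|---|
| 50:50 | 90% | 83% |
| 43:57 | 89% | 83% |
| 80:20 | 77% | 67% |
| 90:10 | 53% | 47% |

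Worked case at 80:20 (1150 and 288 patients): the SEs are 0.0260 and 0.0144, so 0.07/0.0260 = 2.69 gives 77% and 0.03/0.0144 = 2.09 gives 67%.

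The unequal splits are assumptions. The 43:57 and 90:10 rows borrow the two adherence figures in the Background section, and 80:20 is illustrative.

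**The case against.** The best defence is that these are wording slips around a sound calculation. Standard proportion 0.95, expected difference 0, margin 3%, one-sided 0.05 and 80% power are all stated and give 653. The planned 1997 comes from the other endpoint. All of that stands. A reader might infer that the mortality sample size cannot be reproduced, and Step 1 shows that it can.

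It can also be said that the detection sentence is a loose lead-in, because the sentences after it disclose a non-inferiority calculation. That softens the error but does not remove it: the sentence makes a claim about statistical significance that the calculation does not address. A reader might go too far the other way and infer that the sample cannot detect any 3-point difference. That is not supported either. In the direction hypothesised under Study objectives (better outcomes with less follow-up), 5% v 2% has 87% two-sided power. The shortfall is in the harm direction, which is the one a safety margin addresses.

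On group sizes, planning for equal groups when the split is unknown is usual, and the cohort takes all consecutive eligible patients, so there is no allocation to alter. That also stands. A reader might infer from the 90:10 row that the study will have about half the stated power. The documents do not support this. The split rests on a surgeons' estimate that the article itself calls a possible overestimate of adherence. Neither adherence figure uses the 16-month definition, and neither is stated to be for patients with a normal first CTA. At the one figure taken from a study, 43:57, almost nothing is lost.

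**Conclusion.** The point holds as an error in stated inputs and in a stated power property, not as an error in N. The 0.97 entry and the 5% gloss are wrong as written; 653 and 1813 follow from 0.95 in both groups. The detection claim is unsupported: the calculation gives 80% power (83% at 719 per group) to exclude a 3-point excess if there is none, against 64% two-sided power to detect a rise from 5% to 8%. The equal-groups assumption deserves a sentence because its effect ranges from negligible near balance to serious at 80:20 and beyond, and the protocol does not establish where the split will fall.

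These results rest on normal approximations for 7-year proportions, the protocol's own event rates, and 1438 analysable patients with a normal first CTA.

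**What to change.** In Sample size and power:

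1. Replace 0.97 with 0.95.
2. Describe 0.95 as 95% freedom from aneurysm-related mortality, that is, 5% aneurysm-related mortality.
3. Replace the detection sentence with: 80% power at 653 per group (83% at 719) to show non-inferiority within 3 points at one-sided 0.05 if there is no true difference. Add that a non-significant log-rank test is not in itself evidence of safety.
4. State that the 90% and 80% figures assume near-equal groups, and give power for a few splits such as those in Step 5, labelled as assumptions and computed with one variance formula.

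The cost is a few sentences. No sample size changes. The power statement reads less favourably only if the groups turn out very unequal.

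### The stated 80% power for aneurysm-related mortality holds only for a crude 7-year proportion with every status known, but the analysis named for the primary endpoints is Kaplan-Meier

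*Protocol article*

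**What the plan says.** All references are to the protocol article.

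- **Sample size and power, error rate.** "We chose a one-sided significance level (non-inferiority) of 0.05".
- **Same section, reference proportion.** "for standard proportion a 95% non-aneurysm-related mortality and thus 5% freedom from aneurysm-related mortality after 7 years: 0.95". The terms are swapped in this sentence. The value used is 0.95 free of aneurysm-related death at 7 years.
- **Same section, margin and result.** The acceptable difference is 3 percentage points. "the expected difference is 0, calculated with a power of 80%. This results in 653 patients per group and 1306 patients in total". Dividing by 0.8 for abnormal first scans and by 0.9 for incomplete data gives 1813.
- **Same section, planned size.** The intervention endpoint needs more patients (719 per group) and sets the total of 1997. The only allowance for lost information in either calculation is that "we expect incomplete data in 10% of the patients".
- **Statistical methods.** The primary endpoints, described there as survival and freedom from intervention, "will be estimated by Kaplan-Meier survival analysis" and compared by log-rank test, with Cox regression for adjustment. Chi-square and Fisher tests appear only for baseline characteristics.
- **Main study endpoint.** Intervention and aneurysm-related mortality, worded as a number of patients.
- **Study procedures.** All-cause mortality is a secondary outcome, and dates of death are verified against the municipal register. No rate of death from other causes is given anywhere.

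**The concern.** The power calculation and the named analysis use different quantities. The sample-size formula treats the 7-year outcome as a yes/no status known for everyone. In a Kaplan-Meier analysis of aneurysm-related death, a patient who dies of something else at, say, year 3 would ordinarily be censored then. That patient contributes nothing to the estimate for years 3 to 7. The variance of the 7-year estimate is then larger than the formula assumes, and the allowances for abnormal first scans and incomplete records do not cover this. Follow-up beyond 7 years does not recover the loss, because the reference proportion is fixed at 7 years.

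Aneurysm-related mortality is the safety endpoint on which any statement that imaging can safely be reduced depends. If its power is overstated, a failure to show non-inferiority could be read as evidence of harm when it reflects imprecision.

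**Working it through.** **1. Reproduce the stated figure.** Inputs from Sample size and power: proportion 0.95 in both groups, margin 0.03, one-sided alpha 0.05 (z = 1.6449), power 80% (z = 0.8416).

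n = (1.6449 + 0.8416)² × 2 × 0.95 × 0.05 / 0.03² = 652.6, so 653 per group. Then 2 × 653 = 1306, 1306/0.8 = 1632 and 1632/0.9 = 1813, all as stated.

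The section also says "Test-expected proportion is then equal to the standard proportion 0.97". With 0.97 in both groups the formula gives 400, so 0.95 is the value behind 653.

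**2. Planned size.** 1997 × 0.8 × 0.9 / 2 = 719 per group.

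**3. Power with every status known.** The variance per patient is 0.95 × 0.05 = 0.0475. At 719 per group, SE = √(2 × 0.0475/719) = 0.0115. Power = Φ(0.03/0.0115 − 1.645) = 83%. At 653 it is 80%.

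**4. Power with other-cause deaths censored.** Assume constant hazards and independent censoring:

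- λ = −ln(0.95)/7 for aneurysm-related death
- μ = −ln(1 − m)/7 for other-cause death, where m is the assumed other-cause mortality by 7 years
- V = 0.95² × [λ/(λ+μ)] × (e^{7(λ+μ)} − 1), the large-sample (Greenwood) variance per patient
- power = Φ(0.03/√(2V/n) − 1.645)

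Example at m = 30%: λ = 0.00733, μ = 0.05095 and V = 0.0572, which is 1.20 times 0.0475. At n = 719, SE = 0.0126 and power = Φ(0.734) = 77%.

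| Assumed m | V / 0.0475 | Power, 719 per group | Power, 653 per group |
|---|---|---|---|
| 0% | 1.00 | 83% | 80% |
| 20% | 1.12 | 79% | 76% |
| 30% | 1.20 | 77% | 73% |
| 40% | 1.31 | 74% | 70% |
| 50% | 1.45 | 70% | 66% |

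Simulation of the same setting agreed within about 1 point.

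**5. Where 719 per group crosses 80%.** The size has room for a variance ratio of 719/652.6 = 1.10. This is reached at m of about 17%. At 653 per group there is no room, because power starts at exactly 80%.

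**6. Sensitivity to the timing of aneurysm-related deaths.** These are Weibull times with 95% free at 7 years, 719 per group and m from 20% to 50%. If deaths come early (shape 0.5), power runs from 81% to 74%. If they come late (shape 2), it runs from 78% to 66%. Administrative censoring between 6 and 11 years, on its own and with constant hazards, costs under 1 point (83.3% to 82.7%).

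**7. Crude reading.** If the 5% is the crude 7-year risk and is compared as a proportion, a patient who died of another cause counts as known to be free of aneurysm-related death. Nothing is lost: 80% at 653 and 83% at 719.

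**The case against.** The strongest reply is that the censoring is an inference. Statistical methods does not name aneurysm-related mortality, does not say how other-cause deaths are handled, and gives no test against the 3-point margin. Its word survival could mean overall survival, where no death is censored. The main endpoint is worded as a number of patients and the sizing uses proportions, which fits a crude risk. Deaths are verified in a register, so that status is largely obtainable. On that reading the plan's arithmetic is correct and there is no loss. In addition, 653 is only a check that this endpoint needs fewer patients than the other. The study plans 719 per group, which starts at 83%, and at 20% other-cause mortality it is one point short of 80%. An article may also leave estimator details to a fuller document.

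Most of this stands, and it makes the finding conditional. It does not remove the finding. The article does name a method for its primary endpoints, and that method is Kaplan-Meier with log-rank and Cox. No comparison of crude proportions and no cumulative-incidence method is named for any endpoint. If survival there means overall survival, the mortality power calculation has no matching analysis at all. On either reading of Statistical methods, the sizing and the analysis do not fit each other.

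A reader might infer that the study is shown to be underpowered for its safety endpoint. The documents do not support that. They contain no other-cause death rate and do not state the censoring, and a crude analysis would keep the stated power. Nor is 653 an arithmetic error, because it is correct for its inputs.

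**Conclusion.** The point holds in conditional form. The 80% at 653 per group (1813 in total) is valid for a crude 7-year proportion with complete status, and the article plans no such comparison. If other-cause deaths are censored in a Kaplan-Meier analysis, the planned 719 per group falls below 80% once other-cause mortality by 7 years exceeds about 17%, and 653 per group falls below it at any other-cause mortality above zero.

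The size rests on 95% in both groups, independent censoring, constant hazards and an assumed mortality range of 20% to 50% that comes from outside the documents. Over that range the shortfall at 719 per group against the stated 80% is between 1 and 10 points, so it is small at the low end. If the conflicting 0.97 applied to both groups, power at 719 would stay above 80% over the same range, but 0.97 does not produce the stated sample size.

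**What to change.** In Sample size and power, say whether 95% is a net (Kaplan-Meier) or a crude proportion, and which estimator the 3-point margin is tested on. Then take one of two routes:

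- **Kaplan-Meier with other-cause deaths censored.** Restate the power at 719 per group under an explicit other-cause mortality assumption, for example about 77%, 74% and 70% at 30%, 40% and 50%. Remove the claim that 653 per group (1813 in total) gives 80%.
- **Crude proportion.** Keep 653 per group at 80% and add that 719 gives 83%. In Statistical methods, name the matching crude-risk (cumulative incidence) comparison for aneurysm-related mortality.

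Whichever route is taken, correct the 0.95/0.97 conflict in the same paragraph so that the inputs match the result.

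The cost is a rewrite of one paragraph and, on the second route, one added sentence in Statistical methods. No extra patients are needed. On the first route the stated power becomes less favourable.
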